#### Data Management

One of the principal investigators (PI) will create the database. Two collaborators will be in charge of entering data under PI supervision and keeping the database uploaded. To ensure participant confidentiality, a registration number will be assigned to each participant. No personal information will be contained in the database. Range checks for data values and regular audits will be conducted to promote data quality.

#### Statistical Methods

Quantitative variables will be presented as mean and standard deviation, unless otherwise stated, and descriptive variables as absolute numbers and percentages. Univariate analysis will be performed using appropriate statistical tests depending on variable distribution. Treatment effect will be analyzed by changes in muscle mass and strength pre- and post-intervention. Changes during follow-up will be assessed by analysis of variance using mixed repeated measures and a one-factor design for the analysis of values over time. The outcomes from the RCT will be analyzed by intention-to-treat and the results over the follow-up period will be reported considering potential scenarios of non-compliance and non-adherence. Additional univariate analyses (e.g., subgroup and adjusted analyses) according to sex, age, and frailty will be performed. Significance level will be set at *p* ≤ 0.05.

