Frailty is very frequent among CKD patients included in the waitlist for deceased donor KT, and post-transplant outcomes are worsened in those frail recipients. Moreover, frailty and poor fitness powerfully predict mortality, kidney graft survival, and healthcare utilization after KT. Thus, we hypothesize that a pre-transplant clinical framework for multimodal prehabilitation interventions including physical therapy, nutritional measures, and psychological support could improve patient retention and compliance, better mitigate the effects of frailty and poor fitness after KT, and improve main outcomes in frail CKD patients.

The main objective of this study is to assess effectiveness, feasibility, and safety of multimodal prehabilitation (exercise, nutritional plans, and psychological advice) in KT candidates in the context of a randomized controlled clinical trial. There are three specific objectives: (1) to study the potential effects of multimodal prehabilitation as a prognostic variable to predict the 90-day primary endpoint based on clinical and functional outcomes achieved in frail and non-frail KT candidates; (2) to assess the feasibility and safety of a multimodal prehabilitation program, with especial emphasis on the exercise component in KT candidates; and (3) to assess differences in exercise capacity, muscle function, functional status, and health-related quality of life in frail and non-frail candidates at 1-year post-KT follow-up.

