## Methods and Analysis

### Trial Design

The FRAILMar Study is a controlled randomized clinical trial in candidates to KT assigned to the intervention group (multimodal prehabilitation) or control group (standard medical care), with an allocation ratio of 1:1, in a superiority framework. Results are stratified by frail and non-frail patient status. The study protocol is described following the Standard Protocol Items: Recommendations for Interventional Trials (SPIRIT) Statement (3).

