### Study Outcomes

All study outcomes are summarized in Figure 1. The **primary endpoint** will be a bad-outcome composite variable assessed at day 90 post-KT, comprising delayed graft function >14 days, never functioning kidney, non-elective readmission before day 90, surgical complications (wound healing problems, obstructive lymphocele, vascular thrombosis, urinary stenosis or leak, acute hemorrhage, immediate re-intervention), discharge to an assisted facility, or all-cause death.

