### Sample Size

Sample size is calculated to identify significant differences in overall bad-outcome in KT recipients. Accepting an α risk of 0.05 and a β of 0.2 in two-sided testing, 38 frail participants (19 in each group, intervention and control) will be necessary to recognize as statistically significant a decrease of 25% in bad outcomes. The sample size has been overestimated to allow potential losses of 20%, requiring a final sample of 46 patients (23 in each group). Similarly, 76 non-frail patients (38 in each group, intervention and control) will be necessary to recognize as statistically significant a decrease of 12.5% in bad outcomes. Given the patient mortality after listing, the potential for exclusion from the kidney transplant waiting list due to medical issues, and the possibility of voluntary drop-out, 20% of potential losses has been considered to estimate a final sample of 92 (46 in each group). Therefore, sample size in the FRAILMar study will be of 138 participants.

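### The Statistical Methods tie the treatment effect to pre/post changes in muscle mass and strength, which conflicts with the day-90 composite that is the primary endpoint and the basis of the sample size

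*Protocol article*

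**What the plan says.** All references are to the protocol article.

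- **Study Outcomes.** The primary endpoint "will be a bad-outcome composite variable assessed at day 90 post-KT". Its components include prolonged delayed graft function, a kidney that never functions, unplanned readmission, surgical complications, discharge to an assisted facility and death. Peripheral and respiratory muscle strength and lean mass are listed under the secondary, mid-term outcomes.
- **Sample Size.** "Sample size is calculated to identify significant differences in overall bad-outcome in KT recipients". The error rates are given as follows: "Accepting an α risk of 0.05 and a β of 0.2 in two-sided testing". The frail stratum is sized on a 25% decrease in bad outcomes: "38 frail participants (19 in each group, intervention and control) will be necessary". The non-frail stratum is sized separately, at 38 per arm, on a 12.5% decrease.
- **Trial Design.** Intervention is compared with standard care "with an allocation ratio of 1:1, in a superiority framework", and results are stratified by frailty.
- **Statistical Methods.** "Treatment effect will be analyzed by changes in muscle mass and strength pre- and post-intervention". The surrounding sentences cover univariate tests chosen by the distribution of the variable, a mixed repeated-measures analysis of variance with a one-factor design for values over time, and intention-to-treat analysis of the trial's outcomes. The composite is not named.
- **Objective 1 (Background and rationale).** The aim is "to study the potential effects of multimodal prehabilitation as a prognostic variable to predict the 90-day primary endpoint".

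**The concern.** A superiority trial needs one answer to the question of which contrast decides whether the treatment worked. Study Outcomes, Sample Size and Trial Design give one answer. The Statistical Methods sentence gives another.

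The Blinding section makes this more than a drafting matter. Only the data analysts are blinded, and the staff who deliver the programme also take part in most assessments. Strength tests depend on effort, and Data Collection Methods takes the best of three attempts for such measures, so encouragement and practice can raise them. Several components of the composite, such as death or a kidney that never functions, are much less open to this. If the muscle result were favourable and the composite were not, the sentence as written would allow the muscle result to be presented as the planned treatment effect.

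Objective 1 adds some ambiguity. A randomised treatment is not a prognostic variable, and the objective should speak of its effect on the endpoint.

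**Working it through.** No arithmetic decides this point. The check sets the statements side by side.

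| | Study Outcomes, Sample Size, Trial Design | Statistical Methods sentence |
|---|---|---|
| Variable | Bad-outcome composite (yes/no) | Muscle mass and strength (continuous) |
| Status | Primary | Secondary, mid-term |
| Timing | Day 90 after transplantation | Before and after the intervention, so before transplantation |
| Contrast | Intervention against control | Change over time; no arm named |
| Basis of sample size | Yes | No |

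**Step 1: is there a second sentence that defines the treatment effect?** Within Statistical Methods, no. The intention-to-treat sentence says how participants are kept in their groups. It names no endpoint, effect measure or contrast. The sentence on univariate tests names no endpoint either.

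**Step 2: does the text elsewhere reach the composite?** In part. The section on discontinuing interventions says that patients who stop remain in an intention-to-treat analysis of the primary endpoint. An analysis of the composite is therefore foreseen, but nothing there says that it is the treatment effect.

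**Step 3: does the text supply a between-arm contrast for the muscle changes?** Not explicitly. The mixed repeated-measures analysis could carry arm as a factor, and the article says that all patients are assessed before and after the exercise period, so control data will exist. The text does not state an arm term. Even with one, these variables would remain secondary.

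**Step 4: what was the trial sized on?** The stated inputs are two-sided α = 0.05, β = 0.2 and decreases of 25% and 12.5% in bad outcomes. No mean, standard deviation or target change for any muscle variable enters the sample size. The totals after losses are 46 + 92 = 138.

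The stated 19 and 38 per arm cannot be confirmed, because no control-arm rate is given. With the pooled two-proportion formula and the decrease read as an absolute difference, the smallest possible requirements are 27 per arm (25% falling to 0%) and 58 per arm (12.5% falling to 0%). An arcsine formula gives 15 and 31 at those same extremes. This is a separate matter and the present point does not depend on it. Whichever formula was used, the calculation concerns the composite.

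**The case against.** The strongest reply is that the article, read as a whole, leaves no doubt about its primary endpoint. The Abstract, Study Outcomes and Sample Size all name the composite, objective 1 refers to the 90-day primary endpoint, and intention-to-treat implies a comparison of randomised groups. The test for the composite may sit in a full protocol or analysis plan that is not shown.

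Much of this stands. Silence about the test would be no finding. The point is a positive statement that attaches the treatment effect to other variables; a later analysis plan would have to contradict it or inherit it.

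The reply also rules out three stronger readings that a reader might infer:

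- **That the plan has outcome switching built in.** The documents do not support this. The composite is prespecified in several places, and one loose sentence shows neither an intention nor a rule to replace it.
- **That the control arm is discarded and time trends are counted in full as treatment effect.** The sentence does not specify a within-arm test, both arms are assessed before and after, and the repeated-measures model leaves room for an arm comparison.
- **That all the muscle measures are exposed to assessor influence.** The Blinding section says most assessments, not all. Lean mass is also measured by DXA at the third baseline visit, which takes place outside the Rehabilitation Department, and a learning effect on DXA is implausible. The worry applies mainly to effort-dependent strength.

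**Conclusion.** The point holds as a conflict within the article. The sentence that says how the treatment effect is analysed names secondary variables, a pre-transplant time frame and no between-arm contrast, against a primary endpoint, a sample size and a design that all concern the between-arm difference in a post-transplant composite. The intention-to-treat wording makes it likely that the composite will be analysed, but it does not say that the composite carries the treatment effect.

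The size of the problem is qualitative: it concerns which result may be called the treatment effect, and no bias can be computed from the documents. The conclusion assumes only that the sentence means what it says. If it was meant to describe secondary outcomes compared between arms, the remedy is the same. The wording of objective 1 is supporting evidence and would not carry the point alone.

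**What to change.** Replace the sentence in Statistical Methods with a statement to this effect:

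- The primary treatment effect is the intention-to-treat difference between randomised arms in the proportion of patients with the day-90 bad-outcome composite, reported with a 95% CI.
- It is estimated within the frail and the non-frail stratum, in line with their separate sizing. Any overall test is stratified by frailty. A single pooled test should not silently replace the stratum-specific comparisons, because the strata were sized on different effects (25% and 12.5%).
- Changes in muscle mass and strength are secondary outcomes and are compared between arms, not within arm.

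Reword objective 1 so that it asks about the effect of multimodal prehabilitation on the 90-day primary endpoint.

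The cost is a change of wording in two places, made before the outcome data are analysed. It needs no new data, visits or patients.

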Demographic and clinical characteristics of participants will be recorded. Anticipated variables to be used in the analysis as potential confounders include frailty assessed with the Fried phenotype (33), malnutrition, sarcopenia, comorbidity burden, personality traits, and mindfulness dispositional traits.

All patients will be assessed before and after the supervised exercise intervention, with follow-up every 6 months until KT and 1 year after KT. Time points for each outcome measurement are detailed in Figure 1.

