### Allocation

**Sequence generation:** A random number generator program will be used to allocate patients to the intervention and control groups for each stratum: non-frail or robust (Fried scores 0–1) and frail (Fried scores 2–5).

**Allocation concealment mechanisms:** Allocation concealment will be ensured as the person in charge of randomization will not release the randomization codes until participants have completed all baseline measurements.

**Implementation:** A clinician blinded to patient identification will generate the allocation sequence, doctors and nurses from the Nephrology department will enroll potential participants, and the physical therapists in charge of assessments A-1 and A-2 will assign participants to the interventions.

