## Discussion

Frailty in CKD patients displays a unique constellation of features that characterize this special population, including muscle wasting, anorexia, protein energy wasting, inflammation, oxidative stress, catabolic/anabolic hormone imbalance, metabolic acidosis, and other cellular alterations. Intervention is essential to improve quality of life for frail CKD patients, regardless of their age. Studies of post-transplant physical therapy intervention have been met with limited success, in large part due to high dropout rates. A pre-transplant clinical framework that provides multimodal prehabilitation interventions including physical therapy, nutritional measures, and psychological support may improve patient retention and compliance, better mitigate the effects of frailty and poor fitness after KT, and improve main outcomes in frail CKD patients.

Prehabilitation is more challenging in KT than in other surgical settings because the transplantation date is usually unknown. Furthermore, not all KT candidates can combine prehabilitation sessions with their HD schedules. Work schedules and geographic distance can also limit participation. In a recent survey, only 25% of HD patients were able to exercise without difficulty; the major barriers for the remaining patients were feeling too tired (55%), shortness of breath (50%), and too weak (49%) (65). If patients were to exercise, they preferred to exercise at home (73%) using a combination of aerobic and resistance training (41%), regardless of modality or age category. Finally, an extremely large sample size would be required to assess long-term outcomes like death or graft loss, as well as other important clinical outcomes that result from increased physical activity (66–68).

The main limitation is the low physical profile of many frail CKD patients, even those scheduled for KT. Consequently, some patients will not consent to undertake the intervention program and the adherence could be low, with high dropout rates. Efforts will be made by the research team to facilitate all logistical requirements and explain the strong potential benefits to the patients and their families. The process of designing the prehabilitation plan will take account of the final users' perspective in order to achieve a realistic, acceptable, user-friendly approach that covers patient needs and preferences and avoids simplistic solutions that ignore the patients' reality.

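### The plan for change over time states no between-arm, baseline-adjusted comparison for the continuous secondary outcomes

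*Protocol article*

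**What the plan says.** Two sentences in the Statistical Methods section of the protocol article govern this point. The first defines the effect: "Treatment effect will be analyzed by changes in muscle mass and strength pre- and post-intervention". The second gives the longitudinal method, by which changes during follow-up are to be "assessed by analysis of variance using mixed repeated measures and a one-factor design for the analysis of values over time". Neither contains an arm term, an arm-by-time interaction or the outcome's baseline value. Adjustment appears later in the paragraph, as an extra: "Additional univariate analyses (e.g., subgroup and adjusted analyses) according to sex, age, and frailty will be performed". The same paragraph promises intention-to-treat analysis of the trial outcomes.

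Four other places set the context:

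- Trial Design describes two parallel arms, "with an allocation ratio of 1:1, in a superiority framework".
- Allocation says that the person in charge of randomisation "will not release the randomization codes until participants have completed all baseline measurements", so every baseline value precedes knowledge of the arm.
- Study Outcomes has patients assessed before and after the supervised programme, "with follow-up every 6 months until KT and 1 year after KT". It names two horizons for secondary outcomes: 6 months after the intervention, and 1 year after kidney transplantation (KT).
- The Discussion notes that "the transplantation date is usually unknown".

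**The concern.** A superiority trial supports a claim about an outcome through the difference between randomised arms. The two governing sentences describe change within patients and a design with one factor over values in time, and they do not say what that factor is. An analyst following them literally could test each arm's change from baseline and report a significant change in the intervention arm as a benefit. Fitness, strength and mood scores can move in both arms for reasons unrelated to the programme, and the control arm is itself encouraged to be active.

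Even if arms are compared, the text does not use the baseline value that is collected anyway, which costs precision in a small trial. In addition, the number of pre-KT visits depends on when a kidney arrives, and a classical repeated-measures ANOVA handles that poorly.

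**Working it through.** The document gives no power or precision figure for the secondary outcomes (its sample size concerns the day-90 composite), so there is no stated figure to reproduce. The check works through the possible readings.

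**Inputs from the document:** 19 per arm (frail) and 38 per arm (non-frail), hence 19 + 38 = 57 per arm overall; two-sided α 0.05 and 80% power, borrowed from Sample Size.
**Assumed, because not given:** baseline-to-follow-up correlation ρ, equal SD at both times, and an exponential waiting time to KT.

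**Reading A: the factor is time, tested within each arm.** Suppose both arms truly change by the same amount, so there is no treatment effect. With ρ = 0.7 the change has SD √(2(1−0.7)) = 0.775 in units of the outcome SD. In 20,000 simulated trials per cell, the probability that exactly one arm shows a significant change was:

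| Per arm | Common change 0.2 SD | 0.3 SD | 0.4 SD |
|---|---|---|---|
| 19 | 0.302 | 0.466 | 0.490 |
| 38 | 0.459 | 0.457 | 0.215 |
| 57 | 0.494 | 0.292 | 0.061 |

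These follow 2p(1−p), with p the chance that one arm is significant. For 19 per arm and 0.2 SD, p = 0.185 and 2 × 0.185 × 0.815 = 0.302. By symmetry, half of each figure is the intervention arm alone, about 3% to 25%. A direct between-arm test of the same data was significant in 4.8% to 5.1% of runs, in either direction.

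**Reading B: the factor is arm, in an arm-by-time mixed-design ANOVA.** With one follow-up time, the interaction is the difference in mean change. Per-patient variances, in units of σ²:

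- change score: 2(1−ρ)
- baseline-adjusted (ANCOVA): 1−ρ²
- ratio: (1−ρ²) / (2(1−ρ)) = (1+ρ)/2

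| ρ | Change | ANCOVA | Ratio |
|---|---|---|---|
| 0.5 | 1.00 | 0.75 | 0.75 |
| 0.7 | 0.60 | 0.51 | 0.85 |
| 0.8 | 0.40 | 0.36 | 0.90 |

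The detectable difference at 80% power is (1.960 + 0.842) × √(2v/n), with v the variance above. At n = 57 per arm it falls from 0.525 to 0.454 SD for ρ = 0.5, and from 0.406 to 0.375 SD for ρ = 0.7.

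**Unequal visits, if the ANOVA is the classical complete-case form.** With an exponential wait of median m months, the share still waiting at t months is 0.5^(t/m). Of patients with a 6-month value, the share lost by also requiring a 12-month pre-KT value is 1 − 0.5^(6/m): 50%, 29%, 21% and 16% for m = 6, 12, 18 and 24. A mixed model that uses all available visits loses none of these 6-month values.

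**The case against.** The strongest reply is that the text need not be read against its authors. *Mixed* repeated measures ordinarily means one between-subject factor with time within subjects, and in a two-arm superiority trial analysed by intention-to-treat that factor is naturally the arm. *Mixed* could also mean a mixed model that accepts unequal visits. An arm-by-time or change-score contrast is unbiased under randomisation. Covariance structure, estimation method and covariates are details that a condensed article may leave to a statistical analysis plan, which may exist and is not shown here.

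Much of this stands, and it rules out several stronger readings that a reader might infer:

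- *The analysis is non-comparative.* The document never says that the one factor is time, so this follows under Reading A only.
- *Patients will be deleted listwise, leaving long waiters.* No such rule is stated. It is a consequence of one form of ANOVA fitted through the later visits.
- *The transplant schedule undermines the pre/post comparison.* The Physical Exercise section takes participants off the waitlist during the programme and returns them after the 12-week assessment, so by design that comparison precedes KT. Only the 6-month and later visits can be thinned.
- *Pre-KT and post-KT values share one time axis.* Mid-term and long-term outcomes are listed separately, and nothing puts them in one model.
- *Unadjusted change scores are planned for every outcome.* Pre/post change is named only for muscle mass and strength.

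The reply does not remove the point itself. The article does more than leave details open: it defines the treatment effect and names a method, and in neither place does it state the arm contrast or use the outcome's baseline. The adjusted analyses it does mention are additional and by sex, age and frailty.

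**Conclusion.** The point holds as an unclear and improvable analysis statement for the continuous secondary outcomes; it does not show that the planned analysis is invalid. Under the reading least favourable to the plan, the result would not be a randomised comparison. Under the more favourable arm-by-time reading, it is valid but has between 1/0.90 = 1.11 and 1/0.75 = 1.33 times the variance of a baseline-adjusted analysis, for an assumed ρ of 0.8 to 0.5. If *mixed* means a mixed model, unequal visits are accommodated, but the contrast and the baseline term are still unstated.

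The correlations and waiting times are assumptions, so these sizes are illustrative. The simulated false-signal rates apply to Reading A alone. The day-90 composite primary endpoint is untouched.

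**What to change.** For the continuous secondary outcomes, replace the two sentences with the following:

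1. A linear mixed model using all available pre-KT visits, with arm, visit, arm×visit, the outcome's baseline value and frailty stratum (the randomisation stratum). Report the between-arm difference, with its confidence interval, at the post-intervention assessment and at 6 months after the intervention.
2. The 1-year post-KT values analysed separately, by ANCOVA on baseline value and frailty stratum.
3. Any within-arm analysis over time labelled descriptive.

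The text should acknowledge that KT ends the pre-KT series, so the mixed model assumes that values missing for this reason are missing at random given the data observed. If a statistical analysis plan already specifies such a model, the article's sentences need only be brought into line with it. The cost is wording and slightly more programming. No new data, visits or patients are needed, since baseline values are already collected before allocation is released.
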